### OMIC Analyses

We considered power to detect correlations between biomarker signals of any type and the CoP. We assumed approximate normality, after data transformation (e.g., log-transformation) and calculated detectable Pearson coefficients for samples using group size *n* = 30 or *n* = 60. We concluded that our design offered 80% power to detect correlations between continuous measures as small as *r* = 0.25–0.48. Additional parameters were included when carrying out power calculations for the transcriptomic analysis to account for variable coverage [e.g., read depth across biosamples using RNASeqPower v1.10 (28)]. Here we considered power to detect differentially abundant transcripts between two groups and estimated within-group standard deviation from preliminary data, as before. We found *n* = 30 would result in 80% power to detect a 2.4-fold difference in the relative abundance of a transcript, while *n* = 60 would result in 80% power to detect 1.4-fold difference, assuming a balanced design.

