## Sample Size/Biostatistical Considerations

The cohort design included careful consideration of statistical power and sample size. Power calculations in the setting of traditional OMIC designs are well-documented (28) and we performed power calculations for OMIC platforms or flow cytometry based on preliminary data (unpublished data). Although we intended our tests of hypothesis to borrow strength across data types, little has been published on statistical power for integrative analyses or cross-platform comparisons, so this characteristic of our design was not taken into account when determining sample size. Power calculations were carried out using group sizes ranging between *n* = 30 or *n* = 60 per group, two-sided significance criterion (alpha) of 0.05, and a target 80% power to detect.

Since preliminary data for flow cytometry were not available, we performed a worst-case power analysis using a real-world published data on the most variable cell subpopulation where a significant difference was still identified comparing healthy, immunosuppressed, and transplant-tolerant individuals (29). This provided a lower bound of the minimum sample size required to detect a significant difference in cell sub-populations that could act as potential biomarkers. We found *n* = 30 would result in 80% power to detect a 2.3-fold difference in the relative abundance of a cell population, while *n* = 60 would result in 80% power to detect 1.8-fold difference, assuming a balanced design.

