## Participant Selection

### Study Sites

In the Gambia, 720 mother-infant pairs (60 per group) will be recruited through delivery rooms at one secondary level care institution; The Kanifing General Hospital and one primary health facility; The Banjullinding Health Center in The Gambia. In PNG, 80 mother-infant pairs will be recruited at Goroka Hospital, the only tertiary hospital in the Eastern Highland Province of PNG. Maternal infant pairs will be recruited within the first 24 h of the infants' life.

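### At n = 60 the plan has 80% power for r of about 0.35, not 0.25; power at r = 0.25 is about 49%

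*Protocol article*

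**What the plan says.** The Sample Size/Biostatistical Considerations section of the protocol article sets the common inputs. "Power calculations were carried out using group sizes ranging between *n* = 30 or *n* = 60 per group", with a "two-sided significance criterion (alpha) of 0.05, and a target 80% power to detect".

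The OMIC Analyses section then turns to correlations between any biomarker signal and the correlate of protection. It assumes approximate normality after transformation and says the authors "calculated detectable Pearson coefficients for samples using group size *n* = 30 or *n* = 60". It concludes that the design gives "80% power to detect correlations between continuous measures as small as *r* = 0.25–0.48".

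The Study Sites section confirms the group size for The Gambia: "720 mother-infant pairs (60 per group) will be recruited". The article gives no pooled n, one-sided test or other alpha for the correlation calculation.

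**The concern.** The smallest detectable Pearson correlation depends only on n, alpha, sidedness and power, and the article prints all four. A reader can therefore check the range directly. The end for n = 30 agrees with its inputs and the end for n = 60 does not.

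This matters because the Background names the correlation between molecular signatures and vaccine-mediated protection as the main outcome measure, and the Study Analysis Plan makes association with anti-HB titre the aim. The other power figures in the article are fold changes between groups, so this sentence alone tells the reader how weak an association with titre the study can find. Post-vaccine samples are taken on day 1, 3 or 7 in separate sub-groups of 60, so n = 60 is the natural unit for a day-specific correlation. A reader who trusts 0.25 would expect a true correlation of that size to be missed one time in five. Within one such sub-group it would be missed about half the time.

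**Working it through.** **Inputs.** Two-sided alpha 0.05, power 80%, and n = 30 or n = 60 (Sample Size/Biostatistical Considerations; OMIC Analyses). Bivariate normality after transformation (OMIC Analyses). No multiplicity adjustment, as in the article.

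**Formula.** Fisher z for one correlation tested against zero:

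r = tanh[(z for alpha + z for power) / √(n − 3)], with 1.960 + 0.842 = 2.802.

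**Upper end, n = 30.** 2.802 / √27 = 2.802 / 5.196 = 0.539, and tanh(0.539) = 0.492. The exact distribution of r gives 0.485. Exact power at r = 0.48 is 79.0%. The stated 0.48 therefore reproduces to within rounding, which also indicates that the two-sided test was the one used.

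**Lower end, n = 60.** 2.802 / √57 = 2.802 / 7.550 = 0.371, and tanh(0.371) = 0.355. The exact method gives 0.352 and a noncentral t approximation 0.345. No method comes near 0.25.

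**Power at r = 0.25, n = 60.** atanh(0.25) = 0.2554; 0.2554 × 7.550 = 1.928; 1.928 − 1.960 = −0.032; Φ(−0.032) = 48.7%. The exact calculation and a simulation of 100,000 data sets both give 49.3%.

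**n needed for r = 0.25.** n = 3 + (2.802 / 0.2554)² ≈ 123.4, so 124 by Fisher z and 123 by the exact method.

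**Could another reading give 0.25?**

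| Reading | Detectable r for the n = 60 end | Detectable r for the n = 30 end |
|---|---|---|
| As stated, two-sided, one group | 0.355 | 0.492 |
| One-sided alpha 0.05, one group | 0.318 | 0.445 |
| Two groups pooled (n = 120; n = 60) | 0.253 | 0.355 |
| Article's figure | 0.25 | 0.48 |

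(Fisher z values.) The one-sided reading misses 0.25 and moves the other end away from 0.48. Pooling two groups matches 0.25 but breaks 0.48. No single reading gives both ends.

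The two-sided 5% critical value of r at n = 60 is 0.254. An observed r of that size is just significant, while a true r of that size has about 50% power. Confusing the two could explain the figure, but that is a guess and nothing here depends on it.

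**Size in variance explained.** 0.352² = 12.4%, against 0.25² = 6.3%.

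**Effect of losses.** The article gives no attrition figure here. If 10–15% were lost by Day 128 (an assumption), 54 to 51 of 60 remain, and the limit becomes tanh(2.802 / √51) = 0.37 to tanh(2.802 / √48) = 0.38.

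**The case against.** The strongest reply is that the sentence speaks of what the whole design offers and never assigns 0.25 to n = 60, whereas the fold-change sentences pair each figure with its n. The design has 12 sub-groups of 60, and the Study Analysis Plan intends signatures by vaccination schedule. Pooling the three draw-day sub-groups gives 180 infants per schedule, for which the detectable r is tanh(2.802 / √177) = 0.21 and power at r = 0.25 is about 93%. Baseline features, which are a stated objective, could be analysed this way. On this view the defect is an unstated pooled n.

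Part of this stands. The half-the-time miss rate applies to a correlation near 0.25 analysed within one sub-group of 60, not to every analysis in the study. The n of 180 is itself before losses and applies to at most three of the four arms: under Termination, Groups 10 to 12 leave after the week-one visit, before the Day 30 and Day 128 titre samples.

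It does not save the sentence. The text ties the calculation to n = 30 or n = 60, mentions no pooling, and has an upper end that matches a single group of 30.

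It is also fair to say that this is discovery work with multivariate integration and a validation cohort, and that the article does not show the sample size was chosen because r = 0.25 was reachable. That limits the consequence but does not make the figure correct.

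**Conclusion.** The lower end of the range is wrong on the article's own inputs. At n = 60 with two-sided alpha 0.05, 80% power corresponds to r of about 0.35. Power at r = 0.25 is about 49%, a shortfall of about 31 points from the stated 80%. The upper end, 0.48 for n = 30, is acceptable rounding.

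The conclusion assumes one Pearson correlation tested at 0.05 under bivariate normality, with all 60 infants contributing. Losses or a stricter alpha for many features would raise the detectable r, so 0.35 is the favourable case. The error concerns a reported power figure; it does not by itself call for a different sample size or allocation.

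**What to change.** In OMIC Analyses, replace 0.25 with about 0.35 and pair each value with its n: r of about 0.35 at n = 60 and about 0.48 to 0.49 at n = 30.

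If 0.25 was meant for pooled groups, say which groups are pooled and give the n (about 123). For baseline features pooled over the three draw-day sub-groups, a separate statement of r of about 0.21 at n = 180 could be added, limited to the arms with titre follow-up and marked as before losses.

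The cost is one sentence and a less favourable figure. No new data or design change is needed.

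### The transcript fold changes stated as detectable at 30 per group (2.4) and 60 per group (1.4) cannot come from one calculation in which only the group size changes

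*Protocol article*

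**What the plan says.** The Sample Size/Biostatistical Considerations section sets the common conditions: "two-sided significance criterion (alpha) of 0.05, and a target 80% power to detect", at 30 or 60 per group.

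The OMIC Analyses subsection then treats RNA sequencing separately. It names RNASeqPower v1.10 and mentions extra parameters for variable coverage, with read depth as the example. The calculation concerns "differentially abundant transcripts between two groups and estimated within-group standard deviation from preliminary data, as before". Neither the depth nor the standard deviation is given. Two results follow in a single sentence, both for a balanced design:

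- at 30 per group: "We found *n* = 30 would result in 80% power to detect a 2.4-fold difference in the relative abundance of a transcript";
- at 60 per group: "n* = 60 would result in 80% power to detect 1.4-fold difference".

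The parallel statement for flow cytometry, in the parent section, gives 2.3-fold at 30 per group and 1.8-fold at 60 per group, with the same power and a balanced design.

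**The concern.** The sentence presents two points on one power curve. Going from 2.4-fold to 1.4-fold is a very large gain in sensitivity for a mere doubling of the group size, and far larger than the gain in the flow cytometry pair.

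The figure for 60 matters most, because Study Sites and Randomization and Blinding plan 60 infants in each of the 12 Gambian groups. A reader will take 1.4-fold as the transcript sensitivity of a comparison between two such groups. If the figure for 30 is the sound one, that sensitivity is heavily overstated, and a 1.4-fold change would be missed about two times in three in such a comparison. If the figure for 60 is the sound one, the planned comparison is described correctly and the figure for 30 is far too pessimistic.

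**Working it through.** **Inputs**

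- Two-sided alpha 0.05, power 80%, n = 30 or 60 per group: Sample Size/Biostatistical Considerations.
- Two groups, balanced, RNASeqPower; fold change 2.4 at n = 30 and 1.4 at n = 60: OMIC Analyses.
- Read depth and within-group coefficient of variation (CV): not stated. They are assumed equal at both sizes and then cancel, so no value is needed.

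**Formula**

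n per group = 2 (z₀.₉₇₅ + z₀.₈₀)² V / (ln FC)², where V = 1/depth + CV² and z₀.₉₇₅ + z₀.₈₀ = 2.8016.

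With alpha, power and V fixed, ln FC is proportional to 1/√n. Hence ln FC(30) / ln FC(60) must equal √(60/30) = 1.414. The same scaling holds, in the normal approximation, for any two-sample comparison of means on the log scale.

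**Control: the flow cytometry pair**

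- ln 2.3 / ln 1.8 = 1.417.
- 2.3 at n = 30 predicts 2.3^(1/1.414) = 1.80 at n = 60. The stated figure is 1.8, so the rule reproduces this pair.

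**The transcript pair**

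- ln 2.4 / ln 1.4 = 0.8755 / 0.3365 = 2.60, against the required 1.414.
- Rounding: the ratio runs from ln 2.35 / ln 1.45 = 2.30 to ln 2.45 / ln 1.35 = 2.99.
- The sample size ratio needed to produce this gain is 2.602² = 6.77, not 2.

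**Variance implied by each figure**, V = n (ln FC)² / (2 × 2.8016²)

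- From 2.4 at n = 30: V = 1.465 (SD 1.21).
- From 1.4 at n = 60: V = 0.433 (SD 0.66).
- Ratio 1.465 / 0.433 = 3.4.

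**What each figure implies for the other**

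| | If 2.4 at n = 30 is right | If 1.4 at n = 60 is right |
|---|---|---|
| Detectable at n = 30 | 2.4 | exp(0.3365 × 1.414) = 1.61 (1.53 to 1.69 over rounding) |
| Detectable at n = 60 | exp(0.8755 / 1.414) = 1.86 (1.83 to 1.88 over rounding) | 1.4 |
| Power for the other printed figure | 1.4-fold at n = 60: 33% | 2.4-fold at n = 30: 99.9% |
| n per group for 80% power on it | 30 × 6.77 = 203.1, so 204 | 60 / 6.77 = 8.9, so 9 |

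The 33% comes from SE = √(2 × 1.465 / 60) = 0.221; 0.3365 / 0.221 − 1.96 = −0.437; Φ(−0.437) = 0.33.

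**Other readings tried**, each starting from 2.4 at n = 30 and giving the fold change at n = 60

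- Noncentral t test, alpha from 0.10 down to 0.0000025: 1.85 to 1.80.
- One-sided alpha at n = 60 only: 1.73.
- 90% power at n = 30 only: 1.71.
- Both of these together: 1.61.
- Scaling FC − 1 instead of ln FC: 1 + 1.4 / 1.414 = 1.99.
- Reading n as a total instead of per group: the ratio is unchanged.

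None reaches 1.4.

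**The case against.** The best defence is that the two runs need not have shared inputs. Depth and CV are both arguments of the software, the text mentions extra parameters for variable coverage, and the preliminary data are unpublished. A variance term about 3.4 times larger in the run for 30 would produce both figures, and the flow cytometry pair, built on different data, cannot rule that out. This is the one real escape. But the text describes no such change and presents the figures as differing only in group size. Depth alone would hardly do it: with a common CV, 1/depth at n = 30 would have to exceed 1.465 − 0.433 = 1.03, a depth below about one read. If the inputs did change, the sentence still misleads as a statement about n.

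The consequence can also be contested. The direction of the error is unknown, and if 1.4 is right the planned size is described correctly. Each vaccine schedule also comprises three subgroups, 3 × 60 = 180 infants. Even with the larger variance, 180 per group would detect exp(0.8755 / √6) = 1.43-fold, with about 75% power for 1.4-fold. That limits the possible harm, but the stated power rests on 30 or 60 per group, not on pooling.

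Finally, the Study Analysis Plan centres on signatures that correlate with or predict anti-HB titre, and the correlation power statement is separate. That is true, and this point leaves the correlation figures alone. The fold changes are nevertheless offered as justification of the design and should be right.

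**Conclusion.** The concern holds. With the alpha, power, balance and software stated, and one variance term for both sizes, the two printed fold changes are incompatible: their log ratio is 2.60 (2.30 to 2.99 over rounding) where 1.414 is required. At least one is wrong as a statement about group size, and the article cannot show whether it is 2.4, 1.4 or both. The coherent pairs that keep one printed figure are 2.4 and 1.86, or 1.61 and 1.4.

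The overstatement of sensitivity at the planned 60 per group (1.4 instead of about 1.86, with 33% power for 1.4-fold) is conditional on the figure for 30 being correct and applies to an unpaired comparison of two groups of 60. The incompatibility itself needs no value for depth or CV, only that they are the same in both runs.

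**What to change.** Rerun RNASeqPower for 30 and 60 per group with one read depth and one within-group CV, state both inputs, and replace the printed pair with the result. If the 2.4 is confirmed, the figure for 60 becomes about 1.86; if the 1.4 is confirmed, the figure for 30 becomes about 1.61; if neither is, give two new values. If different inputs were deliberately used for the two sizes, say so, give them, and show both group sizes under each set. The log fold changes at 30 and 60 should then stand in a ratio of about 1.41, which is a quick check before release.

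The cost is one rerun of an existing calculation and one revised sentence. The correction does not by itself alter enrolment, allocation or study conduct.

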## Ethical Considerations

Ethical approvals have been obtained for the core study in The Gambia from The Gambia Government/MRCG Joint Ethics Committee (Scientific Coordinating Committee number: 1513); for the validation study in PNG from the PNGIMR Institute Review Board (IRB number: 18.12) and the protocol has been approved by the PNG Medical Research Advisory Committee (IRB number 18.14). Ethical approval has also been obtained from the Boston Children's Hospital Institutional Review Board (IRB-P00024239).

## Participant Selection

### Study Sites

In the Gambia, 720 mother-infant pairs (60 per group) will be recruited through delivery rooms at one secondary level care institution; The Kanifing General Hospital and one primary health facility; The Banjullinding Health Center in The Gambia. In PNG, 80 mother-infant pairs will be recruited at Goroka Hospital, the only tertiary hospital in the Eastern Highland Province of PNG. Maternal infant pairs will be recruited within the first 24 h of the infants' life.

### Rationale for Selection of Participants

As infection is most prevalent in the newborn, the study will target this most vulnerable group to help improve our understanding of vaccine-induced cellular and molecular signatures associated with vaccine-induced correlate of protection i.e., anti-HBs Abs.

## Informed Consent

### Community Consent

Community consent will be sought prior to the commencement by providing information to individuals in the communities served by the participating health centers. Village heads and key opinion leaders in the communities will be engaged in large community meetings during which information regarding the study will be provided and opportunities given to ask questions, in line with previous practice at the MRCG and PNGIMR.

### Individual Consent

Women presenting for antenatal care in the 2nd or 3rd trimester of pregnancy will be approached at the antenatal care clinic and given information regarding the study using a detailed informed consent document. Individuals expressing interest in participating will then be provided with a copy of the informed consent document (Appendix) to take home to discuss with their partners or other significant decision maker in the family. Opportunities will be given to ask questions including the provision of contact details to allow potential participants to reach members of the study team after the clinic visit. Follow-up contact will then be made with each potential participant to verify spousal assent, as male members of the family are typically key decision makers in this setting. In addition, families will be asked to confirm if other members of the household need to assent including grandparents of the child in question.

When the mother of the potential participant presents in labor or shortly following delivery, the consent signature will be obtained, and eligibility assessed. Written consent will be obtained from biological mothers of participants in each mother-infant pair only. The consent process will continue throughout the study with confirmation of willingness to continue participation at each contact.

## Future Use of Stored Samples

Written informed consent will also be sought for the future use of left-over biological samples for studies which would require approval by the relevant ethics committees.

## Inclusion/Exclusion Criteria

### Maternal

Healthy women delivering at term will be recruited into the study. Inclusion and exclusion criteria are as detailed below.

#### Inclusion

Reported gestation of at least 37 weeks

Spontaneous vaginal delivery

Written informed consent.

#### Exclusion

Antibiotic use in the week prior to delivery

HIV or HepB positive—Rapid test done in labor or shortly after delivery

TB Diagnosis in mother or family member in the past 6 weeks

Severe intrapartum condition such as severe pre-eclampsia

Physicians assessment of high risk or previous contraindicative obstetric history such as multiple early neonatal deaths.

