#### Exclusion

Previous vaccination with any EPI vaccine

Major known congenital malformation

Apgar score <8 at 5th min.

Physician assessment of potential high-risk infant including significant risk factors for sepsis/morbidity (such as maternal symptoms suggestive of urinary tract infection in the peri-partal period), or macrosomia (birth weight above 4 kilograms).

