## Safety Considerations and Oversight

### Risks and Benefits

We recently reported major cellular and molecular changes which occur over the first week of life demonstrating a dynamic baseline (17). For this reason, we will have a delayed vaccination group in order to distinguish basic immune ontogeny signatures from vaccine-induced changes.

To minimize risks, we will carefully screen mothers and infants to avoid any risk for the infants included in the delayed vaccination group by the following measures: (a) only newborns to HB-sAg negative mothers will be included; (b) any women with history of tuberculosis (TB) or TB contact will be excluded; (c) BCG vaccination is recommended for any time before 3 months of age and infants within the delayed vaccination group will be vaccinated within 10 days of birth. There is indeed evidence to suggest that delayed BCG vaccination may actually be beneficial (30). The continued recommendation for birth doses of the vaccine is to ensure coverage and avoid missed opportunities for vaccination during contact with a health facility. Polio vaccine is recommended at birth in The Gambia and will be delayed by a maximum of 10 days for all infants in our cohort. This infection has not been diagnosed in The Gambia for over 20 years. The risk posed from this slight delay is therefore considered minimal.

Overall, the Ethics Committees have determined that the study to pose minimal risk to participants, consisting of transient pain when drawing blood and possibly mild discomfort during the rectal swab. Rare complications could include bleeding from or inflammation/infection of puncture sites.

There are no direct benefits for the individual participants other than access to care at the research facility allowing for closer surveillance and higher likelihood of detecting illness early. Participants excluded due to maternal HepB positivity will have the added benefit of accessing the HepB vaccine within 24 h after birth from the study team. Despite being recommended by WHO, this practice is not yet uniformly carried out in many low-income countries including The Gambia and PNG, and largely depends on whether the child is born during working hours vs. the weekend and/or late night. In addition, in The Gambia vaccinations given after the tradition of infant naming at the age of 7 days of age is a common local practice also contributing to delayed vaccinations in the real-life setting.

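### The risk section promises a wider TB exclusion for the delayed-vaccination infants than the maternal eligibility list delivers

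*Protocol article*

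**What the plan says.** The Maternal subsection of Inclusion/Exclusion Criteria introduces its lists with "Inclusion and exclusion criteria are as detailed below". The exclusion list then gives a single TB item: "TB Diagnosis in mother or family member in the past 6 weeks".

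The Risks and Benefits section justifies having a delayed-vaccination group. It states that "we will carefully screen mothers and infants to avoid any risk for the infants included in the delayed vaccination group by the following measures", and names three. Measure (a) is that only infants of HBsAg-negative mothers enter. Measure (b) is that "any women with history of tuberculosis (TB) or TB contact will be excluded". Measure (c) is that "BCG vaccination is recommended for any time before 3 months of age" and that "infants within the delayed vaccination group will be vaccinated within 10 days of birth".

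**The concern.** The two TB rules differ. The eligibility list looks back 6 weeks; the risk section has no look-back limit and applies to any woman with such a history. The second rule is offered as a named safeguard for newborns whose birth vaccines are deliberately withheld.

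If staff screen to the list, the risk section overstates the protection these infants have. If staff screen to the risk section, the published criteria misdescribe who was eligible. Two sites in two countries are meant to follow harmonised procedures, and as written they could apply different rules. What is at stake is who may be randomised to delayed BCG and whether the stated safeguard is accurate. The statistical results are not at stake.

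**Working it through.** No published figure needs reproducing. The check is a comparison of the two rules, followed by one allocation fraction.

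**Step 1: the rules side by side**

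| Situation | TB item in the maternal exclusion list | Measure (b), Risks and Benefits |
|---|---|---|
| Mother's own TB, diagnosed within 6 weeks | Excluded | Excluded |
| Mother's own TB, diagnosed earlier | Not excluded | Excluded |
| Family member's TB, diagnosed within 6 weeks | Excluded | Excluded, if that person is a contact |
| Family member's TB, diagnosed earlier | Not excluded | Excluded, if that person is a contact |
| TB in a contact outside the family | Not excluded | Depends on what contact means; not defined |

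The second row alone establishes the conflict and needs no reading of the word contact. The last row is conditional, because the risk section does not say whether contact extends beyond the family.

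**Step 2: is there a reconciling rule elsewhere?** Four other provisions could narrow the gap:

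- The Maternal subsection asks for healthy women. A woman with past, treated TB may qualify.
- Screening includes taking a detailed medical history. That may reveal past TB, but it excludes nobody unless a rule says so.
- The maternal list has "Physicians assessment of high risk or previous contraindicative obstetric history". This is discretionary and does not name TB.
- The infant list has "Physician assessment of potential high-risk infant including significant risk factors for sepsis/morbidity". This is also discretionary and does not name TB.

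None of them states the rule in measure (b).

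**Step 3: chance of the delayed arm once enrolled.** Under Randomization and Blinding, eligibility is assessed before assignment, so an admitted pair cannot be steered away from the delayed arm.

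- The Gambia: 12 groups of 60 (Randomization and Blinding), of which Groups 10 to 12 are delayed (Termination). 3 × 60 / 720 = 180/720 = 0.25.
- Papua New Guinea: 4 groups of 20, taking one of the four as delayed. 20/80 = 0.25.

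This fraction is only the allocation ratio. It does not measure how many pairs are affected, and no TB frequency is given from which to estimate that number.

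**The case against.** The best reply is that the risk section is narrative and measure (b) is shorthand for the eligibility item. Both name the same two elements, the mother's own disease and exposure to another case, and the Maternal subsection presents its list as the detailed criteria. On that reading staff have one clear rule, and the only fault is a dropped time qualifier. This reading is possible, but it does not remove the problem. Measure (b) covers any woman with such a history and stands as a separate safeguard. If the 6-week rule is the real one, the section overstates the protection.

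A second reply is that an article condenses a fuller protocol, and that the screening form and procedures are not shown. That explains a missing definition of contact, and it means nobody can say from the article how screening is actually done. It does not explain two stated rules that differ.

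The third reply concerns size, and it largely stands. BCG is delayed by at most 10 days, well inside the window the section cites. The section also refers to evidence that later BCG may be beneficial, and it notes that vaccination after the naming tradition at 7 days is common in The Gambia. The ethics committees judged the study to be of minimal risk. The short delay therefore carries much of the protection. Even so, the protocol lists the TB exclusion as a measure in its own right alongside the short delay, so it should be stated correctly.

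**Conclusion.** The inconsistency is real and should be corrected. The firm part is the time window: a mother with her own TB diagnosed more than 6 weeks before is excluded by one statement and not by the TB item in the other. Older TB in a family member falls in the same gap if that person counts as a contact. Contact outside the family does so only on a wider reading of the term.

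A pair in the gap faces a 0.25 probability of the delayed arm at either site, assuming one of the four Papua New Guinea groups is the delayed one. The number of such pairs is unknown and expected to be small, and the absolute risk to each infant is small. No estimate, test or sample size depends on the point. The documents do not show which rule was intended.

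**What to change.** Choose one rule and state it identically in both places.

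- **If the broader safeguard is intended:** change the TB item in the maternal exclusion list to any maternal history of TB or any known TB contact, define contact (household, family or wider, and over what period), and make sure the screening form carries the same wording. This costs one line in the list, a check of the form and slightly more screen failures.
- **If the 6-week rule is intended:** restate measure (b) in Risks and Benefits with the 6-week limit and the restriction to the mother and family members. This costs one phrase and does not change recruitment.
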